#### Sub-group analyses (heterogeneous treatment effects, HTEs)

Acknowledging that certain groups may benefit substantially while others may benefit far less, exploratory heterogeneous treatment effect (HTE) analyses are planned (Aim 3). The goal of the HTE analyses is to explore if there are subgroups for whom swallowing interventions have varied impact. For hypothesis-generating analyses, HTEs will be assessed by testing the treatment arm by subgroup interaction. Analyses are planned according to two potential sources of HTE [34]: the patient and provider**.** For parsimony, a likelihood ratio test will examine proposed HTEs simultaneously. Irrespective of their significance, the subgroup effects will be reported (with 95% confidence intervals) to be assessed in terms of clinical significance.

We have identified several participant subgroups for whom differences in treatment response or swallowing outcomes may exist. Preliminary data suggest superior swallowing outcomes in younger patients [10], those with HPV-associated cancers [68–70] those with no prior surgery [68], those who receive lower doses of RT [10], those who avoid chemotherapy [68, 71] and who avoid prophylactic feeding tube placement [9]. Each of these classifications will be examined as relevant subgroups in the exploratory HTE analysis, as justified below:

### Sample size calculation

Sample size calculations, based on a 2-sample t-test, assume 952 patients enrolled with 1:4 allocation to RE-ACTIVE (Arm 1, *n* = 190) and PRO-ACTIVE arms (Arms 2 and 3, *n* = 381 per group). The attrition factor is set at 5% because the primary endpoint can be ascertained without clinical encounter. Thus, the resultant sample size estimated is 180 in Arm 1, 361 in Arm 2, and 361 in Arm 3. For the primary comparison (Hyp 1.1) of Arm 1 (*n* = 180) versus the combined Arms 2 and 3 (*n* = 722), assuming ITT analysis with type 1 error probability of 0.05 (two-sided) yields 80% power to detect a small effect size of .23 SD for duration of feeding tube use. For the analysis of Hyp 1.2 in the gate-keeper approach, we will compare intensity of PRO-ACTIVE therapies (Arm 2 versus Arm 3, *n* = 361 per group), assuming type 1 error probability of 0.05 (two-sided), we have 80% power to detect again a small effect size of 0.21 SD for the primary endpoint of feeding tube duration. We expect the t-test will not be sufficient as the primary analysis given it does not allow for covariate adjustment. Therefore, we will apply the multiple linear regression model as the primary analysis for Aim 1. The power calculation conducted assuming t-tests for analysis of hypotheses 1.1 and 1.2 and deriving a sample of 952 patients remain sufficient for the linear model because by adjusting for variables associated with the mean response, the distribution of the residuals is expected to improve. Therefore, the power for the same hypothesized difference in the primary outcome attributed to treatment in the regression framework will be at least as much as for that for the t-test.

For the secondary analysis (Aim 2) in the gate-keeper approach, we will compare intensity of PRO-ACTIVE therapies (Arm 2 versus Arm 3, *n* = 361 per group), assuming type 1 error probability of 0.05 (two-sided), we have 80% power to detect again a small effect size of 0.24 SD for PROs and VFS measures. The attrition factor for the secondary analysis is set at 26% because they are more prone to attrition due to required clinical visits and survey responses required from participants. As an exception, feeding tube dependence at 3-months uses an attrition factor of 5%, for the same rationale as the primary endpoint.

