## Aims and hypotheses

To address this evidence gap, the primary aim (Aim 1) of the PRO-ACTIVE trial is to compare the effectiveness of PRO-ACTIVE versus RE-ACTIVE swallowing interventions among patients with HNC planned to undergo RT. We hypothesize that at 12-months post radiotherapy the combined PRO-ACTIVE therapies are more effective than RE-ACTIVE therapy (Hyp 1.1); and, if so, that more intensive PRO-ACTIVE (EAT + EXERCISE) is superior to less intensive PRO-ACTIVE (EAT) (Hyp 1.2). Effectiveness will be measured based on reduced duration of feeding tube dependency, a pragmatic outcome valued by diverse stakeholders including patients, caregivers and clinicians [13, 21, 25, 26].

The second aim (Aim 2) of the PRO-ACTIVE trial is to compare the relative benefit or harm of PRO-ACTIVE to RE-ACTIVE swallowing intervention on all secondary outcomes at both 3- and 12- months post radiotherapy, namely: swallowing impairment, maximum interincisal opening (trismus), swallowing-related QOL, symptom burden, self-reported pneumonia, malnutrition and mood disorder, cancer coping strategies, diet level, feeding tube rates, weight loss, hospitalization and/or emergency department (ED) presentation. In addition, the second aim will compare the benefit on reduced duration of feeding tube presence at 3-month post radiotherapy. Our hypothesis for this second aim is that the combined PRO-ACTIVE interventions will result in better secondary outcomes at 3- and 12- months following the completion of RT (Hyp 2.1). As in our primary aim, for each secondary outcome for which PRO-ACTIVE is superior, dose response of the PRO-ACTIVE arms will be examined hypothesizing the more intensive therapy as superior (Hyp 2.2).

The third aim (Aim 3) of the PRO-ACTIVE trial is to explore the relative benefit or harm of the PRO-ACTIVE and RE-ACTIVE swallowing interventions in relevant subgroups according to the following: age, tumor site, prior surgery, radiation dose, chemotherapy use, and prophylactic feeding tube use. Our hypothesis for this third aim is that all interventions will be more effective in the following higher risk subgroups: older age; non-HPV related cancer sites; prior surgery; higher radiation dose; chemotherapy (yes); and, prophylactic feeding tube insertion (yes).

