The randomization of participants will be stratified by participating site using a centralized, automated and concealed process conducted by the Data Coordinating Center (DCC). Participants and therapy providers will not be blinded; however, clinical raters and data analysts will be blinded to the study arm to minimize bias. Eligible patients will be randomized in a 1:2:2 allocation to RE-ACTIVE (Arm 1, *n* = 190) and each of the PRO-ACTIVE arms (Arms 2 and 3, *n* = 381 per group). All patients will be followed to 12 months post-RT. The main intention to treat analysis will compare duration of feeding tube dependence post-RT. The study schemata is shown in Fig. 1.

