**Patient Reported Outcomes (does not require clinic visits)**										
Trigger PRO***			(X)	(X)	(X)	(X)	(X)	(X)		
MDADI	X							X^i^	X	X
Tube PRO	X			XX		XX		XX	X^j^	X^k^
MDASI-HN	X			X		X		X	X	X
Exercise Diary			X*	X*	X*	X*	X*	X*	X	X
MOD^g^	X								X	X
Self-Report Pneumonia^h^	X								X	X
CBI-I	X								X	X
EQ-5D-5L	X								X	X

(X) Only for untriggered RE-ACTIVE arm participants

XX Only for Triggered RE-ACTIVE Arm 1, PRO-ACTIVE EAT and PRO-ACTIVE EAT + EXERCISE Arm 3 participants

X* Only for Triggered RE-ACTIVE Arm 1 and PRO-ACTIVE EAT + EXERCISE Arm 3 participants

^a^ X-Ray involved. Requires central lab review

^b^ randomization completed within 72 h of eligibility verification by completion of central VFS review

^c^ Per chart abstraction by coordinator; if missing in chart, by coordinator contact

^d^ Validated clinic interview along with study specific questions administered by SLP/Clinician (or by a research coordinator if no clinic visits or missed in clinic)

^e^ RT plan DICOM archived to central database

^f^ Conducted by Speech Language Pathologist and only for participants assigned to PRO-ACTIVE arms. Participants in RE-ACTIVE arms who are triggered will begin swallowing therapy according to the EAT-EXERCISE model in arm 3 (PRO-ACTIVE EAT + EXERCISE) within 3 treatment days

^g^ to be completed at select sites only

^h^ administered as part of MOD

^i^ completed at the end of RT

^j^ to be completed every 2 weeks for first 3 months after RT within ±3 days

^k^ to be completed monthly within ±7 days

**Coordinator review of trigger status of RE-ACTIVE participants

***Participant review of PRO dependent trigger items (i.e. tube feed and MDASI #16 choke item)

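### The Aim 2 power statement (80% at 0.24 SD for PROs) does not apply to the MOD-based outcomes, which are collected at select sites only

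*Protocol article*

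**What the plan says.** All references are to the protocol article.

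- **Sample size calculation.** The Aim 2 sentence concerns one contrast: "For the secondary analysis (Aim 2) in the gate-keeper approach, we will compare intensity of PRO-ACTIVE therapies (Arm 2 versus Arm 3, *n* = 361 per" arm. The error rate is given as "assuming type 1 error probability of 0.05 (two-sided"), and the conclusion is "we have 80% power to detect again a small effect size of 0.24 SD for PROs and VFS measures". On losses it says "The attrition factor for the secondary analysis is set at 26" per cent, because clinic visits and survey responses are needed. One departure is named: "As an exception, feeding tube dependence at 3-months uses an attrition factor of 5" per cent. The MOD is not excepted.
- **Aims and hypotheses.** The Aim 2 outcomes include "self-reported pneumonia, malnutrition and mood disorder, cancer coping strategies, diet level", with no limit by site.
- **Secondary outcomes, item 5.** The MOD is described as a patient-reported inventory with nutrition, pulmonary and psychology parts.
- **Table 1, Schedule of Activities.** The MOD sits under the patient-reported outcomes with footnote g, "to be completed at select sites only". Footnote h says that self-reported pneumonia is given within the MOD, so it carries the same site limit.

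**The concern.** One power figure is printed for all patient-reported outcomes of Aim 2, with a single exception. Three of the named Aim 2 outcomes come from an instrument that some sites never administer. Participants at those sites cannot contribute to those outcomes, whatever their follow-up.

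The secondary endpoints section says that these outcomes are analysed regardless of the primary result, so they will receive their own inference. A reader who sees no difference between EAT and EAT+EXERCISE on malnutrition, mood or pneumonia could weigh it against a printed 80% power that those comparisons may not have.

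**Working it through.** **Inputs**
- Enrolled per PRO-ACTIVE arm: "each of the PRO-ACTIVE arms (Arms 2 and 3, *n* = 381 per group" (Overview of trial design).
- Attrition for secondary outcomes 26%, two-sided alpha 0.05, effect 0.24 SD, two-sample t-test (Sample size calculation).
- Share *f* of participants at MOD sites: **not given, so assumed**. Randomization is stratified by site, so the same *f* is used in both arms. The 26% attrition is assumed to hold at MOD sites too.

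**Formulas** (normal approximation, checked against the exact t-test)
- Power = Φ(0.24 × √(n/2) − 1.960)
- Effect detectable with 80% power = (1.960 + 0.842) × √(2/n)

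**Step 1: reproduce the printed figure**
- 381 × 0.74 = 282 per arm. 0.24 × √141 = 2.850, less 1.960 = 0.890, so power is 81.3% (exact t-test 81.2%). Detectable effect 2.802 × √(2/282) = 0.236 SD.
- If 26% is instead taken off the printed 361: 361 × 0.74 = 267 per arm, power 79%, detectable effect 0.24 SD.
- With the printed 361 itself, power at 0.24 SD is 90% and the detectable effect is 0.21 SD, so 361 is not the basis of the claim.

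The claim thus rests on about 267 to 282 per arm, from all sites after 26% attrition.

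**Step 2: how much slack there is**

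The exact t-test needs about 273.5 per arm for 80% power at 0.24 SD. 273.5 / 281.94 = 0.97, so the MOD sites would have to hold about 97% of participants for the full 80%. If the eleven sites enrolled equally (an assumption), leaving out just one gives 381 × 0.74 × 10/11 = 256 per arm and about 77% power.

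**Step 3: the MOD-based outcomes over an assumed range**

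n per arm = 381 × 0.74 × *f*; exact t-test.

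| Assumed share *f* | n per arm | Power at 0.24 SD | Effect detectable with 80% power |
|---|---|---|---|
| 90% | 254 | 77% | 0.25 SD |
| 75% | 211 | 69% | 0.27 SD |
| 50% | 141 | 52% | 0.33 SD |
| 25% | 70 | 29% | 0.48 SD |

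These figures are for outcomes analysed as scores. If self-reported pneumonia is analysed as yes or no, the smaller n applies equally, but the SD scale does not carry over directly.

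**The case against.** **The share is unknown, so the loss may be trivial.** This stands as a limit on size. At a 90% share the detectable effect is 0.25 SD, hardly different from the printed value. A reader might infer that the MOD comparisons can detect only a clearly larger effect; the article does not support that as a fact, because it depends on the share. The direction is certain all the same.

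**The planned analysis is better than a t-test.** The secondary endpoints section plans ANCOVA with the baseline value, and Table 1 schedules the MOD at baseline. Dividing 0.24 by √(1 − r²), an assumed baseline correlation r of 0.5 gives about 81% power at a 75% share, 64% at 50% and 37% at 25%; with r = 0.7, a 50% share gives about 80%. So some or all of the loss may be recovered. But the printed figure is a t-test figure and takes no such credit, and no correlation is given.

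**The 26% attrition already covers it.** This does not stand. That allowance is for participants who miss visits or surveys, not for sites that never give the instrument.

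**Interpretation is already protected.** In part. The plan reports 95% confidence intervals and uses minimal clinically important differences, which lessens the risk of misreading. It does not make the printed power statement correct.

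**A condensed article need not list the MOD sites.** Agreed, and their absence is not the point. The point is that a printed claim is broader than the article's own Table 1 allows.

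**A stronger reading to avoid.** A reader might infer that power for PRO-ACTIVE versus RE-ACTIVE on the MOD outcomes also falls short of a stated 80%. The sample size section states no Aim 2 power for that contrast. With all sites and 26% attrition (190 × 0.74 = 141 versus 762 × 0.74 = 564) it has only about 72% at 0.24 SD, because of the 1:4 allocation. A shortfall there cannot be laid to the select-site restriction alone.

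**Conclusion.** The point holds as a matter of scope. The arithmetic behind 80% at 0.24 SD is sound for outcomes collected at every site with 26% attrition. It does not extend to malnutrition, mood and self-reported pneumonia, which come from the MOD at select sites. On the article's own t-test basis, the full 80% is kept only if those sites hold about 97% of participants. Below that, power for EAT versus EAT+EXERCISE runs from 77% at a 90% share down to 29% at a 25% share. The true value cannot be fixed from the article.

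The conclusion rests on equal shares in the two arms, on 26% attrition at the MOD sites, and on no credit for baseline adjustment. These are secondary outcomes; the primary endpoint and the sample size of 952 are untouched. Severity: minor.

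**What to change.** - In the sample size section, restrict the statement of 80% power at 0.24 SD to PRO and VFS measures collected at all sites.
- Add one sentence for the MOD-based outcomes (malnutrition, mood, self-reported pneumonia), with the number expected from the select sites and the effect detectable with 80% power at that number. If half the participants were at MOD sites, that would be 0.33 SD on the t-test basis. If credit is taken for ANCOVA, state the assumed baseline correlation.
- In the aims section, mark these three outcomes as collected at select sites only.

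The cost is wording: no extra participants or procedures. The downside is a less favourable stated detectable effect for these secondary outcomes.

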The largest threat of missing data is non-random loss of outcomes data for the primary endpoint. Missing data for the primary endpoint is extremely unlikely because it is a simple variable that can be ascertained in clinic or remotely via telephone/web interview of the patient. Non-random missing data is more likely for outcomes requiring clinic examination (i.e., videofluoroscopy) for which we have estimated attrition at 26% based on prior longitudinal work from the investigators [38]. For outcomes missing in > 10% of patients, we will consider multiple approaches. One method we may employ is inverse probability weighting approach to account for statistical uncertainty due to missingness. Another option we will explore is multivariate imputation using chained equations [66]. When similar inferences are derived from complete case analysis and imputation, we will report complete case analysis results for simplicity and transparency.

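### The Aim 2 power sentence prints n = 361 per group, the 5%-attrition number, although its 0.24 SD fits the roughly 282 per group left after the stated 26% attrition (minor; wrong as written)

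*Protocol article*

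**What the plan says.** All figures are in the protocol article, section Sample size calculation, unless stated otherwise.

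- Calculations use a two-sample t-test with 952 enrolled: 190 in RE-ACTIVE and 381 in each PRO-ACTIVE arm. After 5% attrition for the primary endpoint these become 180, 361 and 361.
- For the primary endpoint both steps are given: 0.23 SD for Hyp 1.1 (180 versus 722) and 0.21 SD for Hyp 1.2 (361 versus 361), each at 80% power and two-sided 0.05.
- For Aim 2: "For the secondary analysis (Aim 2) in the gate-keeper approach, we will compare intensity of PRO-ACTIVE therapies", again with 361 per group. At two-sided alpha 0.05 the claim is: "we have 80% power to detect again a small effect size of 0.24 SD for PROs and VFS measures".
- The next sentence reads "The attrition factor for the secondary analysis is set at 26" per cent. One outcome is exempt: "As an exception, feeding tube dependence at 3-months uses an attrition factor of 5" per cent.
- The Primary endpoint section gives the same rate for "outcomes requiring clinic examination (i.e., videofluoroscopy) for which we have estimated attrition at 26" per cent.
- Aims and hypotheses, together with Secondary endpoints, put the comparison of RE-ACTIVE with combined PRO-ACTIVE (Hyp 2.1) first. The intensity comparison (Hyp 2.2) follows only for outcomes where PRO-ACTIVE is superior.

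**The concern.** The same n, alpha, power and test cannot yield a detectable effect of 0.21 SD for Hyp 1.2 and 0.24 SD for Aim 2. The n in the Aim 2 sentence also conflicts with the attrition stated directly after it. A reader would take it that PRO and VFS comparisons are expected to rest on 361 analysable patients per PRO-ACTIVE arm, when the plan's own attrition implies about 282. The printed number is 28% too high (361/282 = 1.28).

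A second, supporting matter is that the paragraph gives sensitivity only for the second step of the Aim 2 sequence. The first step sets RE-ACTIVE, the smallest arm, against the pooled arms. It has a larger detectable effect, and no figure is given for it.

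**Working it through.** **Inputs.** From Sample size calculation: two-sided alpha 0.05; power 80%; two-sample t-test; 190/381/381 randomised; attrition 5% (primary) and 26% (secondary).

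**Formulas.** Working in SD units with the normal approximation:

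- Detectable effect = (1.960 + 0.842) × √(1/n1 + 1/n2).
- Power at effect d = Φ(d/√(1/n1 + 1/n2) − 1.960).

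The noncentral t gives the same values to within about 0.0005 SD and 0.2 percentage points of power.

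**Step 1: reproduce the primary figures.**

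- 190 × 0.95 = 180.5 and 381 × 0.95 = 361.95, printed as 180 and 361.
- Hyp 1.1: 2.802 × √(1/180 + 1/722) = 2.802 × 0.0833 = 0.233 SD. Stated: 0.23.
- Hyp 1.2: 2.802 × √(2/361) = 2.802 × 0.0744 = 0.209 SD. Stated: 0.21.

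Both reproduce, so the method is the one the authors used, and 361 is the number after 5% attrition.

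**Step 2: the Aim 2 sentence as printed (361 per group, 0.24 SD).**

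- Detectable effect at 80% power: 0.209 SD, as for Hyp 1.2.
- Power at 0.24 SD: Φ(0.24/0.0744 − 1.960) = Φ(1.26) = 89.7%, not 80%.
- 80% power at 0.24 SD needs 273 per group.

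The sentence does not reproduce.

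**Step 3: apply 26% attrition.** There are two possible bases.

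| Base for the 26% | n per group | Detectable effect, 80% power | Power at 0.24 SD |
|---|---|---|---|
| Randomised 381 | 381 × 0.74 = 281.9, so 282 | 2.802 × √(2/282) = 0.236 SD | 81.3% |
| Already reduced 361 | 361 × 0.74 = 267.1, so 267 | 2.802 × √(2/267) = 0.243 SD | 79.2% |

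Both round to the printed 0.24 SD. The effect size already carries the 26%, and only the n was not updated.

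**Step 4: the first-step test, Hyp 2.1, at 26% attrition.**

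- 190 × 0.74 = 140.6, so 141; 762 × 0.74 = 563.9, so 564.
- Detectable effect: 2.802 × √(1/141 + 1/564) = 2.802 × 0.0942 = 0.264 SD.
- Power at 0.24 SD: Φ(0.24/0.0942 − 1.960) = Φ(0.59) = 72%.
- With the 26% taken off 180 and 722 instead (133 versus 534): 0.271 SD and about 70%.

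These are unadjusted t-test figures, on the same footing as the article's own. The Secondary endpoints section plans ANCOVA with the baseline value where one exists. With baseline-outcome correlation r, the detectable effect in unadjusted SD shrinks by √(1 − r²). The document gives no r. Purely as an assumption, r = 0.3 to 0.5 would bring 0.264 SD to about 0.25 to 0.23, and power at 0.24 SD to about 76% to 84%. Hyp 2.2 would gain in the same proportion, so the ordering of the two tests does not change.

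**The case against.** The strongest reply is that the planners' result is right. The 0.24 SD reflects 26% attrition and only a number in parentheses is out of date. Correcting it changes no effect size, test, decision rule or enrolment target, and it concerns secondary outcomes. That stands, and it is why the point is minor.

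It could also be said that 361 is the number before secondary attrition. That does not rescue the sentence. The 361 is already net of 5%, and for Hyp 1.2 the same section uses 361 as the analysed number. This reading is, however, the reason the base of the 26% needs confirming. The 5% exception does not help either, because it covers 3-month feeding tube dependence while the sentence is about PROs and VFS measures.

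On Hyp 2.1, the article is a condensed document and need not give power for every secondary hypothesis. That is fair, so the missing figure is a supporting note and not an error. The case for adding it is that the section reports both steps for Aim 1, and that for Aim 2 the step left out is the less sensitive one.

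Some stronger readings are tempting but not supported:

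- That 0.24 SD is too optimistic for Arm 2 versus Arm 3. It is not; it fits the number expected after attrition.
- That the plan claims 80% power at 0.24 SD for PRO-ACTIVE versus RE-ACTIVE. The sentence is limited to Arm 2 versus Arm 3 and claims nothing for Hyp 2.1.
- That null secondary results would be misread, or that the DSMB relies on the figure. Secondary endpoints plans 95% confidence intervals and interpretation against minimal clinically important differences, and the DSMB's described task is review of adverse events of special interest.
- That the MOD sample is materially too small. The Table 1 footnote says "to be completed at select sites only", so a smaller n is a fair inference, but the sites are not counted and its size cannot be computed.

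**Conclusion.** Wrong as written, and minor. In the Aim 2 power sentence, 361 per group cannot stand with 80% power at 0.24 SD: it gives 0.209 SD, or about 90% power at 0.24 SD. The stated effect size agrees with the stated 26% attrition, at about 282 per group (0.236 SD) or 267 (0.243 SD). The error is thus in the n alone, and no power is lost for Arm 2 versus Arm 3.

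As a supporting observation, Hyp 2.1 is less sensitive than the figure shown: about 0.26 SD, or about 72% power at 0.24 SD. This rests on 26% attrition in every arm and an unadjusted t-test. Baseline-adjusted ANCOVA would improve it by an amount the document does not let one compute.

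The primary endpoint figures reproduce, and the target of 952 is not in question.

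**What to change.** In Sample size calculation, Aim 2 paragraph:

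1. Replace 361 with about 282 per group (26% off 381) and keep 0.24 SD for Arm 2 versus Arm 3. The sponsor should confirm that the 26% applies to the randomised 381 and not to 361, which would give 267.
2. Preferably add the first-step figure: with about 141 versus 564, 80% power for about 0.26 SD for Hyp 2.1 by unadjusted t-test, noting that the planned baseline adjustment is expected to improve on this. If the other base is confirmed, the numbers become about 133 versus 534 and 0.27 SD.
3. State that 361 per group applies only to feeding tube dependence at 3 months, the 5% exception.

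The cost is a text correction. Enrolment, tests, decision rules and the primary sample size do not change.
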